## Abstract

**Background:**

Observational studies have suggested that a high respiratory exchange ratio (RER) is associated with the occurrence of postoperative complications. The study’s primary objective is to demonstrate that the incidence of postoperative complications is lower in an interventional group (patients monitored using a hemodynamic algorithm that incorporates the RER) than in a control group (treated according to standard practice).

**Methods:**

We shall perform a prospective, multicenter, randomized, open-label, superiority trial of consecutive patients undergoing major noncardiac surgery (i.e., abdominal, vascular, and orthopedic surgery). The control group will be treated according to the current guidelines on standard hemodynamic care. The interventional group will be treated according to an algorithm based on the RER. The primary outcome will be the occurrence of at least one complication in the 7 days following surgery. The secondary outcomes will be the length of hospital stay, the total number of complications per patient, the 30-day mortality, the total intraoperative volume of fluids administered, and the Sequential [sepsis-related] Organ Failure Assessment (SOFA) score and laboratory data measured on postoperative days 1, 2, and 7. A total of 350 patients will be included.

**Discussion:**

In the operating theater, the RER is potentially a continuously available, easy-to-read, indirect marker of tissue hypoperfusion and postoperative complications. If the RER does predict the occurrence of tissue hypoperfusion, it will help the physician to provide personalized hemodynamic management and limit the side effects associated with excessive hemodynamic optimization (volume overload, vasoconstriction, etc.).

**Trial registration:**

ClinicalTrials.gov NCT03852147. Registered on February 25, 2019

**Supplementary information:**

The online version contains supplementary material available at 10.1186/s13063-020-04879-x.

## Administrative information

The order of the items has been modified to group similar items (see http://www.equator-network.org/reporting-guidelines/spirit-2013-statement-defining-standard-protocol-items-for-clinical-trials/).

## Introduction

### Background and rationale {6a}

For many years, it was accepted that hemodynamic optimization during major noncardiac surgery was associated with lower rates of perioperative morbidity and mortality. This effect was based on maximization of blood flow (related to cardiac output (CO)), tissue perfusion (related to blood pressure), and thus oxygen delivery (DO_2_) to the tissues [1]. Given that surgery is associated with an increase in oxygen consumption (VO_2_), it can lead to a mismatch between DO_2_ and VO_2_; the body’s metabolism becomes partially anaerobic, with tissue hypoperfusion and then postoperative complications [2]. In this context, the international guidelines now recommend hemodynamic optimization in major noncardiac surgery [3, 4]. This approach is based on the use of fluids, vasopressors, and inotropic drugs. All these medications can trigger adverse reactions, which limits their benefits. Indeed, a few recent studies failed to find a clinical benefit of hemodynamic optimization [5–7]. Similarly, a recent meta-analysis found that hemodynamic optimization did not have medical benefit and was associated with adverse events (such as fluid overload) [8]. There are several possible explanations for these results. Firstly, anesthesia procedures and surgical techniques have improved. Secondly, it has been suggested that hemodynamic optimization does not prevent the onset of anaerobic metabolism [5, 8]. Anaerobic metabolism is thought to be triggered by an increase in VO_2_ and a fall in DO_2_. In such a case, all the determinants of DO_2_ (the hemoglobin level, oxygen saturation, and CO) should be maximized in order to meet the VO_2_ demand. Thirdly, the POMO study demonstrated a beneficial effect of hemodynamic optimization only in patients who attained a VO_2_ value close to that measured preoperatively [5]—suggesting the need for individualized hemodynamic optimization. Fourthly, the postoperative morbidity essentially concerns patients with a low anaerobic threshold (an altered baseline VO_2_), i.e., metabolically fragile patients for whom a DO_2_ maximization strategy could be beneficial [8–10]. Taken as a whole, these results and observations suggest that the risk/benefit balance for hemodynamic management can only be achieved by personalized optimization in identified patients with baseline factors that favor anaerobic metabolism.

There is a large body of literature data on variables that can be used to diagnose and track the DO_2_/VO_2_ balance and changes in tissue perfusion. Most of these variables are derived from blood analyses. The literature data on the various parameters’ value for diagnosing anaerobic metabolism are contradictory [11–15]. Based on the physiological knowledge of VO_2_, DO_2_, and CO_2_ production (VCO_2_), the respiratory quotient is known to be a noninvasive parameter reflecting the balance between DO_2_ and VO_2_ and thus anaerobic metabolism [16]. The respiratory quotient is widely used in physiology and cardiology. In the operating theater, the respiratory quotient can be approximated by measuring the respiratory exchange ratio (RER: the gradient between the inhaled/expired CO_2_ and O_2_ fractions and the minute ventilation). The RER reflects the body’s energy metabolism and anaerobiosis [17]. In a model of hemorrhagic shock, changes in the RER reflect the mismatch between VCO_2_ and VO_2_ and thus anaerobic metabolism. Moreover, treatment of the shock corrected the RER [18]. We recently demonstrated that in major noncardiac surgery, the RER is predictive of hyperlactatemia and the occurrence of postoperative complications [19, 20]. Thus, the RER may identify patients with VO_2_/DO_2_ mismatch and who might benefit from maximization of DO_2_. Given that the inhaled and exhaled fractions of O_2_ and CO_2_ are systematically measured in intubated-ventilated patients in the operating theater, the RER is readily available in all anesthetized patients. It might be of value to additionally consider the RER for individualized hemodynamic management. RER monitoring might limit the occurrence of adverse events associated with excessive hemodynamic optimization (volume overload) by selecting only patients who would be likely to benefit from this optimization strategy.

Thus, we hypothesized that individualized hemodynamic management based on continuous noninvasive measurement of the RER would lower the occurrence of postoperative complications because it provides information on the development of the VO_2_/DO_2_ imbalance and limits excessive hemodynamic treatments.

### Objectives {7}

The study’s primary objective will be to demonstrate that a hemodynamic optimization algorithm based on the RER will lower the incidence of at least one postoperative complication (defined according to the European guidelines) in the 7 days following surgery.

The secondary objectives will be to demonstrate a decrease in the length of hospital stay, the incidence of each complication, the arterial lactate level at the end of the procedure, and mortality at 30 days in patients in the RER group.

### Trial design {8}

We are conducting a prospective, open-label, randomized, controlled, comparative, multicenter superiority study of two groups of patients (Fig. 1).

**Fig. 1 Fig1:**
[figure not shown]
Patient disposition

## Methods: participants, interventions, and outcomes

### Study setting {9}

The study will take place in four university medical centers (Amiens University Medical Center, Lille University Medical Center, Caen University Medical Center, Dijon University Medical Center) and a general hospital (Valenciennes General Hospital).

The list of study sites can be obtained from the Clinical Research and Innovation Directorate at Amiens University Medical Center (CHU Amiens- Picardie), [name], France.

### Eligibility criteria {10}

#### Inclusion criteria

Abdominal, orthopedic, or vascular surgery with general anesthesiaAdult patientsAmerican Society of Anesthesiology Physical Status score ≥ IIEstimated duration of surgery > 2 hAt least two of the following co-morbidities: age > 50, high blood pressure, cardiomyopathy, ECG abnormality, pulmonary edema, smoking, stroke, arteritis, insulin-dependent or noninsulin-dependent diabetes, ascites, chronic kidney failureWritten consentAffiliation with a social security scheme

#### Noninclusion criteria

Severe untreated arterial hypertensionChronic renal failure on dialysisAcute heart failureAcute coronary syndromeRenal vascular surgeryCardiac surgeryPermanent laparoscopyPreoperative acute circulatory failureRefusal to participatePregnancyGuardianship, curatorship, or incarcerationLocoregional anesthesia (spinal and epidural anesthesia)Acute respiratory distress syndrome (PaO_2_/FiO_2_ ratio < 300)Chronic respiratory insufficiency with home oxygen therapyParticipation in another clinical study

### The pre-inclusion (enrollment) visit and the associated consenting process {26a}

The pre-inclusion visit must be carried out by an investigator named in the protocol. It will take place during the pre-anesthesia consultation (PAC). All participants who meet the inclusion criteria during the study will be asked to participate in the study. The investigating physician will inform the patient about the study and will answer any questions concerning the study’s objectives, constraints, foreseeable risks, and expected benefits. He/she will also specify the patient’s rights as part of this research and will check the eligibility criteria. Copies of the study information sheet and the consent form are then given to the patient by the investigating physician.

Once the patient has received this information, he/she will be given time to think about whether he/she wishes to participate. The investigating physician is responsible for obtaining the patient’s written, informed consent. The consent form must be signed *before any clinical or paraclinical study procedures* be performed. If the patient agrees to participate, the patient and the investigator write their first and last names clearly and then date and sign the consent form. The various copies of the study information sheet and the consent form are distributed as follows:

A copy of the study information sheet and a copy of the signed consent forms are given to the patient.

The original copies are kept by the investigating physician (even if the patient moves during the course of the research) in a safe place that cannot be accessed by third parties.

At the end of the inclusion period or (at the latest) at the end of the research, a copy of each consent form shall be forwarded to the sponsor or its representative; the investigators will be told in a timely manner how these forms should be forwarded.

### Additional consent provisions for collection and use of participant data and laboratory specimens {26b}

In the context of this research, no additional clinical or paraclinical examinations (i.e., beyond those normally applied for this type of surgery) will be performed.

### Instructions for preparation of requests for an ancillary study

Written informed consent must be provided by each participant in future ancillary studies, if the data collection request is not covered by the informed consent process for the main clinical study. A copy of the institutional review board’s (IRB’s) letter of approval for future ancillary studies will be sent to the OPHIQUE clinical trial’s Data Monitoring Committee. If a separate consent form is required for the ancillary study, a copy of the signed ancillary study consent form for each study participant must be included in the OPHIQUE clinical trial’s records. A data file tracking all signed ancillary consent forms must be maintained by the ancillary study, and an electronic copy of that file must be delivered to the OPHIQUE trial’s Data Monitoring Committee.

### Interventions

#### Explanation for the choice of comparators {6b}

In the control group, the patients’ hemodynamic parameters are managed according to international and national guidelines by maintaining blood pressure with norepinephrine, optimizing the stroke volume by fluid challenge, and (if necessary) administering dobutamine [3, 4] (Fig. 2).

**Fig. 2 Fig2:**
[figure not shown]
Algorithm for patient management in the control group

Cardiac output is optimized firstly by fluid challenge (maximization) and secondly (in the absence of preload dependency) by intravenous administration of dobutamine to obtain a cardiac index (CI) greater than 2.5 l min^−1^ m^−2^. Dobutamine is administered with an electric syringe pump via a dedicated peripheral venous access. The dose of dobutamine (3 mg per kg body weight) is diluted in the syringe to give a total volume of 50 ml. The initial administration rate is 2.5 ml h^−1^ or 2.5 gamma kg^−1^ min^−1^. If there is no change in the CI, the administration rate is increased in increments of 2.5 ml h^−1^ up to a maximum of 10 ml h^−1^ or 10 gamma kg^−1^ min^−1^. The dobutamine infusion will be decreased if the heart rate rises above 100 bpm or increases by more than 40% of the baseline value.

The systolic arterial pressure (SAP) is maintained at more than 10% of the reference value by continuous intravenous administration of norepinephrine, if necessary. The mean initial infusion rate will be 0.05 μg/kg/min, and the infusion rate will be titrated to maintain the target SAP. The treatment is administered during the operative period only and begins with the induction of anesthesia. Next, the targets are:
A hemoglobin level greater than 10 g dl^−1^, using blood transfusionA pulse oxygen saturation (SpO_2_) value greater than 95%, using a recruitment maneuver, increased FiO_2_, and titration of the positive end-expiratory pressure (Fig. 2)

#### Intervention description {11a}

The RER is calculated from the continuous measurement of inspired and expired gases on the anesthesia ventilator (expressed in %): the inspired fraction of oxygen (FiO_2_), end-tidal fraction of oxygen (FetO_2_), inspired fraction of CO_2_ (FiCO_2_), end-tidal fraction of CO_2_ (FetCO_2_), expired volume (Ve), and inspired volume (Vi). The value is averaged over a 5-min moving window.

Assuming that Vi = Ve during mechanical ventilation in a closed circuit:
$$ {\mathrm{VCO}}_2\ \left(\mathrm{ml}\ {\min}^{-1}\right)=\mathrm{Ve}\times \left({\mathrm{FetCO}}_2-{\mathrm{FiCO}}_2\right) $$$$ {\mathrm{VO}}_2\ \left(\mathrm{ml}\ {\min}^{-1}\right)=\mathrm{Ve}\times \left({\mathrm{FiO}}_2-{\mathrm{FetO}}_2\right) $$

Thus:
$$ \mathrm{RER}={\mathrm{VCO}}_{2/}{\mathrm{VO}}_2=\left({\mathrm{FetCO}}_2-{\mathrm{FiCO}}_2\right)/\left({\mathrm{FiO}}_2-{\mathrm{FetO}}_2\right) $$

An RER greater than 1.0 indicates anaerobic metabolism [19], and so DO_2_ must be increased. This increase depends on the hemoglobin level, the arterial oxygen saturation, and the CO (Fig. 2).

Cardiac output is optimized firstly by fluid challenge (maximization) and secondly (in the absence of preload dependence) by intravenous administration with dobutamine to obtain a CI greater than 2.5 l min^−1^ m^−2^. Dobutamine is administered with an electric syringe pump via a dedicated peripheral venous line. The dose of dobutamine (3 mg per kg body weight) is diluted in the syringe to give a total volume of 50 ml. The initial administration rate is 2.5 ml h^−1^ or 2.5 gamma kg^−1^ min^−1^. If there is no change in the CI, the administration rate is increased in increments of 2.5 ml h^−1^ up to a maximum of 10 ml h^−1^ or 10 gamma kg^−1^ min^−1^. The dobutamine infusion will be decreased if the heart rate rises above 100 bpm or increases by more than 40% of the baseline value.

The SAP is maintained at more than 10% of the reference value by continuous intravenous administration of norepinephrine, if necessary. The mean initial infusion rate will be 0.05 μg/kg/min, and the infusion rate will be titrated to maintain the target SAP. The treatment is administered during the operative period only and begins with the induction of anesthesia.

Other objectives are:
A hemoglobin level greater than 10 g dl^−1^, using blood transfusionA SpO_2_ greater than 95%, using a recruitment maneuver, increased FiO_2_, and titration of the positive end-expiratory pressure

If RER is lower than 1.0, SAP must be maintained at more than 10% of the reference value by the intravenous continuous administration of norepinephrine (Fig. 3).

**Fig. 3 Fig3:**
[figure not shown]
Algorithm for patient management in the interventional group

To both avoid extreme clinical practices and minimize interference with the trial intervention, study investigators will be strongly encouraged to apply standard measures, as follows:
Induction of general anesthesia with the use of propofol 2–3 mg kg^−1^, sufentanil 0.2 μg kg^−1^, and cisatracurium 0.15 mg kg^−1^. Inhaled anesthetics or target-controlled infusion of propofol will be used to maintain general anesthesia with a target bispectral index of between 40 and 60, along with intravenous perfusion of sufentanil at 0.1 to 0.2 μg kg^−1^ per hourMechanical ventilation, with a tidal volume of 6–8 ml kg^−1^ predicted body weight, a positive end-expiratory pressure between 5 and 10 cmH_2_O, a FiO_2_ that maintains oxygen saturation ≥ 95%, and the respiratory rate adjusted to maintain an end-tidal CO_2_ between 30 and 35 mmHgThe core body temperature is maintained at 36.5 °CPeroperative use of epidural analgesia is authorizedPostoperative epidural analgesia is authorized

#### Criteria for discontinuing or modifying allocated interventions {11b}

The study may be discontinued for an individual patient if the latter (or the person designated by the patient) so desires or if decided by the investigator. Every effort will be made to comply with the study protocol. However, the clinician in charge of the patient may deviate from these instructions at any time if he/she considers it necessary. He/she must note this decision and the reason for it in the case report form. If the study is discontinued, no provision is made for patient replacement. Likewise, patients having discontinued the study for whatever reason will receive standard care for the surgery and disease in question.

#### Strategies to improve adherence to interventions {11c}

The coordinating investigator will ensure good adherence to the intervention via the following measures:
Visits to study centers in order to train study staff in how to monitor the RER in the operating theater (readings, measurements, analysis, and the pathological threshold)Visits to study centers to explain the collection of primary and secondary outcomes and the follow-up visits (on postoperative day (POD)1, POD2, POD7, and POD30)The hemodynamic optimization protocol is identical to that used in routine care in the operating theaterStudy centers will be regularly contacted by phone in order to ensure good compliance with the research protocol and to answer any questions

Throughout the hospital stay, it is the study team’s responsibility to ensure the proper, timely assessment of outcome measures (including timely visits by the investigator).

#### Relevant concomitant care permitted or prohibited during the trial {11d}

The clinician in charge of the patient’s care may deviate from these instructions at any time if he/she considers it necessary. He/she must note this decision and the reason for it in the case report form. Both treatment groups have access to standard care.

#### Provisions for post-trial care {30}

If the study is discontinued, no provision is made for patient replacement. Likewise, patients having discontinued the study for whatever reason will receive standard care for the surgery and disease in question.

This research is covered by an insurance policy issued by the *Société Hospitalière d’Assurance Mutuelles* insurance company ([name], France; policy reference 147 731 RC RECH). In accordance with the provisions of Article L1121-10 of the French Public Health Code, the policy covers for nonnegligent harm associated with the study. The policy includes cover for additional health care, compensation, or damages whether awarded voluntarily by the sponsor or through claims pursued in the courts. Incidents judged to arise from negligence (including those due to major protocol violations) are not covered by the study’s insurance policy.

#### Outcomes {12}

The primary study outcome is the proportion of patients in the RER group (vs. the control group) with at least one complication within the 7 days following surgery. Complications were defined according to the guidelines issued by the European Society of Anaesthesia and the European Society for Intensive Care Medicine [21].

##### Neurological complications

Stroke, documented on CTMental confusion and disorientation in space and time, according to the Confusion Assessment Method for the ICU

##### Respiratory complications

Acute respiratory distress syndrome (defined as polypnea > 25/min, involvement of the accessory respiratory muscles, or a pH < 7.25), acute lung injury (defined as respiratory distress with a PaO_2_/FiO_2_ ratio < 300 or a PaO_2_ < 80 mmHg under a high-concentration mask), or adult respiratory distress syndrome (defined as respiratory distress with a PaO_2_/FiO_2_ ratio < 200 mmHg)Pulmonary embolism, defined as the presence of one or more emboli in the arterial vessels of the nonoperated lung when CT angioscopy is performedProlonged (> 24 h) orotracheal intubationRepeated orotracheal intubation

##### Cardiovascular complications

Acute systolic heart failure confirmed by echocardiographic impairment of the left ventricular ejection fraction vs. the preoperative baselineAcute right heart failure confirmed by echocardiographic impairment of right systolic and/or diastolic functionAcute pulmonary edema with fluid overload confirmed by a clinical examination and echocardiography and that leads to medical treatmentAcute circulatory insufficiency, defined as treatment with catecholamines (epinephrine, dobutamine, phosphodiesterase inhibitor, levosimendan, and norepinephrine)Postoperative myocardial damage: troponin I or T elevation above the 99th percentileMyocardial infarction, defined as an elevation in cardiac enzymes (creatine phosphokinase myocardial band, troponin T, or troponin I) plus the appearance of a new Q-wave, ST-segment elevation, or ECG repolarization disorderSupraventricular rhythm disorders, defined as the occurrence of atrial flutter or complete arrhythmia by atrial fibrillation and confirmed by ECGVentricular rhythm disorders, defined as the occurrence of ECG-confirmed ventricular tachycardia

Acute renal failure, defined as a postoperative increase of at least 50% and/or 26.5 μmol/l in the creatinine level vs. the preoperative baseline and/or diuresis of less than 0.5 ml kg^−1^ h^−1^ over 6 h (the KDIGO International Society of Nephrology definition) [22]

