### Study timeline for participants

### Sample size {14}

According to the literature data, the postoperative complication rate in the target population is between 30 and 50% [24]. The inclusion of 170 patients in each arm would show that RER-based hemodynamic optimization reduces these complications in a clinically significant manner (by a third; from 50% in the control group to 35% in the interventional arm). These calculations were performed with an alpha risk of 5%, a power of 80%, and a complication rate of 50% in the control arm.

Furthermore, an interim analysis is planned halfway through the inclusion process. Hence, the final study population should be 344 patients. Based on these results and after taking account of potential loss to follow-up, we plan to include 350 patients (175 per arm). If 175 patients are included in each arm, the threshold for statistical significance in a one-sided test will be set to *p* < 0.003 (according to the Lan and Demets spending function, using the seqdesign SAS procedure). Premature study termination for efficacy could thus be considered.

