### Assignment of interventions: blinding

#### Who will be blinded {17a}

Although the operating anesthetists cannot be blinded to group assignments, much attention will be given to ensuring strict blinding during the postoperative, data collection, and data analysis periods. The surgeons and ICU physicians and nurses are blinded to group allocation. Only the anesthetist in charge of the patient during the surgery will be aware of the group allocation.

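### Two primary-outcome components, catecholamine treatment and transfusion, have no scoring rule for algorithm treatment that spans the end of surgery

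*Protocol article*

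**What the plan says.** Outcomes {12} makes a patient an event if he or she is found "with at least one complication within the 7 days following surgery". The components are then written out one by one. Under Cardiovascular complications, acute circulatory insufficiency is "defined as treatment with catecholamines (epinephrine, dobutamine, phosphodiesterase inhibitor, levosimendan, and norepinephrine"). Under Hemorrhagic complications, transfusion of red cells, platelets or plasma stands as a complication in its own right. Neither entry has a start time, a duration, an indication or an exclusion for treatment begun in theatre.

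The algorithms use some of the same treatments. In both arms systolic pressure is supported "by continuous intravenous administration of norepinephrine, if necessary", dobutamine may be given towards a cardiac index target ("Dobutamine is administered with an electric syringe pump via a dedicated peripheral venous access" in the control text, with near-identical wording for the RER arm), and transfusion is used towards a hemoglobin target. Both descriptions also set a limit: "The treatment is administered during the operative period only and begins with the induction of anesthesia".

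The arms differ in what triggers treatment. In the RER arm the increase in oxygen delivery is tied to an RER above 1.0. For the other case the text says "If RER is lower than 1.0, SAP must be maintained" and names only norepinephrine.

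**The concern.** One component is enough to make a patient a primary-outcome event. A norepinephrine infusion being weaned in recovery, or a unit started in theatre and finished afterwards, is treatment given after surgery and so meets the definition as written. Such a patient would be counted for receiving the study's own intraoperative treatment, whether or not an organ complication followed.

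If this happens equally often in both arms, the contrast is diluted. If it happens unequally, part of the observed difference reflects which algorithm treatments were running at the end of surgery. Blinded assessment is no remedy, because a blinded assessor who applies the definition correctly still scores the carried-over infusion as an event.

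**Working it through.** **1. The two periods side by side.** Algorithm treatment: from induction, operative period only. Outcome window: the week after surgery. Treatment that stops with the operation falls outside the window and is not counted. Treatment that runs across the boundary is inside the window, and no sentence says how to score it. The end of the operative period is not defined, and under {11b} and {11d} the clinician may depart from the instructions at any time.

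**2. Which items overlap.** Norepinephrine, dobutamine and transfusion towards a hemoglobin target appear in both the algorithms and the outcome list. Epinephrine, levosimendan, phosphodiesterase inhibitors, platelets and plasma appear only in the outcome list.

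**3. Can it be separated later?** As listed in {18a}, the intraoperative record holds total amounts of norepinephrine and dobutamine and the number of blood products. Stop times are not listed.

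**4. The plan's own figure.** Inputs from Sample size {14}: "from 50% in the control group to 35% in the interventional arm", alpha 5%, power 80%; the two-sided test is from the primary analysis section. With pooled variance and mean rate 0.425:

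n = [1.960·√(2·0.425·0.575) + 0.842·√(0.50·0.50 + 0.35·0.65)]² / 0.15² = 169.3, so 170 per arm, as stated.

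At 175 per arm the null and alternative standard errors are 0.05285 and 0.05224. Power = Φ[(0.15 − 1.960·0.05285)/0.05224] = Φ(0.889) = 81.3%.

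**5. Equal carry-over (assumed; the documents give no rate).** Let c be the share of otherwise event-free patients counted only because of carried-over treatment. The observed rate is p + (1 − p)·c.

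| c | Control | RER | Difference | Power, 175 per arm |
|---|---|---|---|---|
| 0 | 50.0% | 35.0% | 15.0 points | 81.3% |
| 5% | 52.5% | 38.25% | 14.25 points | 76.6% |
| 10% | 55.0% | 41.5% | 13.5 points | 71.6% |
| 20% | 60.0% | 48.0% | 12.0 points | 61.6% |

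**6. Unequal carry-over (assumed), in either direction.**
- No true effect, 50% in both arms, c = 15% control and 5% RER: 57.5% vs 52.5%. The chance of a significant result favoring RER is Φ[(0.05 − 1.960·0.05318)/0.05312] = Φ(−1.021) = 15.4%, against a nominal 2.5%.
- Planned effect, c = 0% control and 10% RER: 50% vs 41.5%, power 35.7%.

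**7. How far overlap with other events shrinks this.** Now read 15% and 5% as shares of all patients. If 80% of carry-over patients have another qualifying event, the additions are 0.15·0.20 = 3 points and 0.05·0.20 = 1 point. The rates become 53% vs 51% and the chance falls to 5.6%. If 70% have another event, the rates are 54.5% vs 51.5% and the chance is 8.1%.

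Steps 5 to 7 use a normal approximation, no loss to follow-up and no interim adjustment.

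**The case against.** The strongest reply is that the periods do not overlap as written: algorithm treatment ends with the operation and complications are counted after it. This stands, and it reduces the problem to a boundary case. A reader might infer that every patient given norepinephrine, dobutamine or blood in theatre becomes an event; the documents do not support that.

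A second reply is that an article condenses, and that the definitions come from a European guideline and a full protocol not at hand. This carries less weight. The list is given in detail, and neighboring items do carry qualifiers: intubation beyond 24 hours, ileus beyond 48 hours, creatinine against a preoperative baseline, and bleeding and myocardial damage labeled postoperative. The two components that overlap with study treatment have no such qualifier.

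Third, a reader might infer that the unblinded anesthetist decides the outcome. The text says only that this person knows the allocation. It also says "The surgeons and ICU physicians and nurses are blinded to group allocation", and the follow-up visits are made by a blinded anesthesiologist who did not manage the patient in theatre. Unblinded influence is therefore limited to what is running at handover.

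Fourth, the contrast between arms is only partly established. The RER algorithm figure is not shown, the RER text lists the hemoglobin target under other objectives without clearly tying it to a high RER, and norepinephrine is conditional on need. Lower transfusion exposure in the RER arm cannot be asserted. A difference in dobutamine and norepinephrine use is plausible from the text.

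Finally, a continuing need for vasopressors can be a genuine sign of circulatory failure, so counting some carry-over is defensible. That argues for a stated rule, not for leaving the case open.

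**Conclusion.** The point holds in a limited form. Two components of the primary outcome lack a rule for treatment that spans the end of surgery, and the literal definitions count it. The result can be dilution or, if drug use at the end of surgery differs between arms, bias in either direction.

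The size cannot be fixed from the documents. The fall from 81% power to 77% or 72% assumes that 5% or 10% of otherwise event-free patients in each arm are affected. If those percentages describe all patients with carry-over, the loss is smaller to the extent that they qualify through other events, which is plausible in so broad a composite. A reader might take the 15.4% in the unequal example as an estimate of false-positive risk. It is not: it rests on invented rates in one chosen direction and drops to about 6% to 8% under heavy overlap. The case for acting rests on the unscored boundary and the low cost of closing it, not on these figures.

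**What to change.** Reconcile the two algorithm descriptions, the outcome window and the two component definitions with one outcome-scoring rule, identical in both arms and fixed before the interim analysis:

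- Define the moment at which the operative period ends and the outcome window opens.
- Count catecholamine treatment only if it is newly started, or restarted after being stopped, once the operative period is over, or if a carried-over infusion continues beyond an interval that the sponsor sets in advance.
- Do not count units whose transfusion began in theatre.
- Record start and stop times, and report intraoperative drugs and blood as treatment exposure.

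This changes scoring only; no treatment rule is proposed.

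The cost is an amendment to the primary-outcome wording during recruitment, added eCRF time fields, a slightly lower event rate and a re-check of patients already randomized (120 according to Trial status, with the interim planned at 175). Anesthesia charts may reveal the allocation, so someone other than the blinded outcome assessor should do the re-check.
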